### **3. Selection of Subjects/population(s) and patient follow up**

This study will include patients affected by IDD in the lumbar spine and persistent LBP that do not respond to conservative treatment, physical and medical (NSAID or opioids), lasting at least 6 months. A pain baseline value over 40/100 on visual analogue scale (VAS) shall be required.

#### **3.1 Inclusion criteria**

- Age between 18 and 65 years.
- Signed informed consent.
- Symptomatic chronic LBP due to moderate IDD [modified Pfirrmann score 3-4 (Pfirrmann et al., 2001), Griffith score 3-7(Griffith et al., 2007)] at max.3 levels of the lumbar spine unresponsive to conservative treatment, physical and medical for at least 6 months. Physical treatment includes physiotherapy. Medical treatments includes NSAID, paracetamol, opioids and myorelaxant. (For more details, see paragraph 1.1.4).
- Annulus fibrosus intact, demonstrated by MRI.
- Pain baseline > 40 mm on VAS (0- 100).NSAID washout of at least 2 days before screening.
- NSAID washout of at least 2 days before screening.

- Painkillers washout of at least 24 hours before screening.
- For females of childbearing potential (see definitions in paragraph 6.5), a negative pregnancy test must be documented at Screening.
- Men and women should use effective contraception during treatment and for at least 24 months after BM-MSD discontinuation. The complete list of contraceptive methods is described in the patient information sheet and in the paragraph 6.5. As a precautionary measure, breast-feeding should be discontinued during treatment with BM-MSD and should not be restarted after discontinuation of BM-MSD.

### 3.2 Exclusion criteria

- Congenital or acquired diseases leading to spine deformations that may upset cell application (scoliosis, isthmus lesion, sacralization and hemisacralization, degenerative spondylolisthesis).
- Spinal segmental instability assessed by dynamic X-Ray.
- Symptomatic facet joints syndrome on MRI (facet joints hyperintensity and hypertrophy evaluated at coronal T2 weighted MRI).
- Prior to the screening visit, has received:
  - Oral corticosteroid therapy within the previous 3 months, OR
  - Intramuscular, intravenous or epidural corticosteroid therapy within the previous 3 months
- Presence of a 4th level with symptomatic IDD (modified Pfirrmann score 3-4, Griffith score 3-7) in the lumbar spine.
- Spinal canal stenosis (Schizas score > B).
- History of spinal infection.
- Lumbar disc herniation and sciatica.
- Endplate abnormality such as Schmorl's Nodes.
- Previous discal puncture or previous spine surgery.
- IDD with Modic II and III changes on MRI images.
- Patients not eligible to the intravertebral disc surgery.
- Patients who have the risk to undergo a surgery in the next 6 months.
- Patients with local infusion device/devices for corticosteroids.
- Obesity with body mass index (BMI in Kg/size in m^2) greater than 35 (obesity grade II).

- Participation in another clinical trial or treatment with another investigational product within 30 days prior to inclusion in the study.
- Abnormal blood tests: hepatic (alanine aminotransferase [ALT] and/or aspartate aminotransferase [AST]  $>1.5 \times$  upper limit of normal [ULN]), renal, pancreatic or biliary disease, blood coagulation disorders, anemia or platelet count of  $<100 \times 10^9/L$ .
- Pregnant or lactating women, or premenopausal women not using an acceptable form of birth control, are ineligible for inclusion. Contraception will be maintained during treatment and until the end of relevant systemic exposure. Additional pregnancy testing will be performed at the end of relevant systemic exposure. The patients will be required to use contraception from initial treatment administration until 24 months after the last dose of study drug.
- In each case of delayed menstrual period (over one month between menstruations) confirmation of absence of pregnancy is strongly recommended. The complete list of contraceptive methods is described in the patient information sheet and in the paragraph 6.5. Positive serology for following infection: Syphilis, HIV, Hepatitis B, or C.
- Contraindication to MRI assessed by the investigator.
- Intolerance or allergy to local anaesthesia.
- Any history of Cancer or immunodeficiency disease.
- Previous transplantation.

### 3.3 Assignment of intervention and blinding

Treatment allocation will be performed 24 hour-a-day online by a central randomization web-service. To randomize a patient, investigators have to login, enter the patient identification, and check the inclusion and exclusion criteria. The patient identification must be unique within all randomizations performed by the randomizing investigator's centre. If everything is entered correctly, a summary of the patient data including the randomization result is shown. For double-blind trial the randomization result will be a treatment code. The PI won't have access to the list of treatment codes used for blinding. Thereby, the treatment code of the patient will be transmitted to local pharmacy.

Blinding or masking will be carried out at all stages of packaging and conditioning for shipping following the treatment allocation. Injections used for all groups will be clear and indistinguishable from each other.

During the application of the cells, in the control group, patients will receive the sterile vehicle using similar procedure by unblinded physician (sham procedure without discal injection). The investigator in charge of patient inclusion and follow-up (different from the physician injecting the cells) and the patient will be blinded.

### **3.4 Patient follow up/Monitoring**

Patient follow up will be performed at screening and randomization and at 6 and 12, for 24 months including Clinical parameters (VAS, ODI, SF-36) and MRI at months 6, 12 and 24.

### **3.5 Withdrawal of the clinical trial**

Patients may always and without specification of reasons withdraw their informed consent and, as a corollary, withdraw from the trial related therapy or the entire clinical trial. The investigator also has the right to withdraw patients in agreement with the sponsor or his delegate.

Patients must be withdrawn from the study under the following circumstances:

- The patient withdraws consent,
- Loss of contact to the patient after 3 reminders,
- Development of an intercurrent illness or condition, which would interfere with the patients continued participation,
- Occurrence of a SAE or an exclusion criteria, which would interfere with the patients continued participation,

Discovery that the subject entered the clinical trial in violation of the protocol or occurrence of a significant protocol violation during the clinical trial. The withdrawal will be decided after notice of the principal investigator and methodologist.

Other reason in the opinion of the investigator that cells should not be injected to prevent the patient from harm.

Any situation that in the opinion of the investigator would pose unacceptable risks to the patient if trial participation is continued.

For any discontinuation the investigator should obtain all required details and should document the date and reason of the premature termination in the CRF.

If the reason for withdrawal is an AE, the specific event will be recorded in the eCRF. The investigator will make thorough efforts to document the outcome.

If a patient is withdrawn from the clinical trial before injection of the cells, it will be replaced by another eligible patient.

If a pregnancy occurs, the patient will be withdrawn from the clinical trial and will be closely followed up.

### **3.6 Lost to follow up**

Investigators should make every effort to minimize the number of patients lost to follow-up and to obtain a maximum of information on patients lost to follow-up, particularly in the search for any AEs. Contact details from investigator centre will be given to each patient. The investigator will call the patient before each scheduled visit. If necessary, the investigator could contact General Practitioner (GP) to reach the patient.

### **3.7 Follow up after discontinuation**

If a patient discontinues from the study for an AE, this patient must be followed up until LPLV and until resolution or stabilization of the event.

As far as possible, in case of withdrawal, the investigator will perform all examinations scheduled for the final study visit, which includes recording of AEs. In any case, the patient will be treated in accordance with standard care in the centre.

### **3.8 Replacement of patients**

Drop-outs will not be replaced (the sample size has been increased assuming a drop-out rate of 10%).

If a patient is withdrawn from the clinical trial before injection of the cells, it will be replaced by another eligible patient.

### **3.9 Follow up after termination**

Patients will continue to be followed according to normal care provided by good clinical practice.

## **4. Measurement of outcomes**

### **4.1 Primary Outcome Measures:**

The clinical response is defined as pain relief of at least 40% and 40 mm decrease on VAS scale between baseline and month 24, or 40% improvement of functional index ODI at month 24 compared to baseline. Chronic LBP is assessed using the VAS pain scale (0 – 100, where 0 represents no pain and 100 represents the worst pain imaginable). ODI scale ranges from 0 to 50 and allows evaluation of disability (0% – 20%: minimal disability; 20% – 40%: moderate disability; 40% – 60%: severe disability; 60% – 80%: crippled; 80% – 100%: bed-bound or exaggerating their symptoms).

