## **2.4 Endpoints**

### **2.4.1 Primary Endpoint:**

- To evaluate the efficacy of intradiscal injection of autologous BM-MSC using the visual analog scale (VAS) and functional status assessed by the Oswestry disability index (ODI) after 24 months of treatment, defining

responders in case of at least 40% improvement in VAS or ODI at month 24 compared to baseline.

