## **7. Statistic analysis planning and power calculation**

Sample size was calculated to have 80% power and 2 balanced groups and according to the literature data (Maher et al., 2017; PopulationReferenceBureau; 2016), a responder rate is expected at 12 months of the order of 30% in controls and 68% for MSC is a delta of 38% between the two groups. To highlight this

difference while justifying a power of 80% and an alpha risk of 5% and within 1:1 ratio, taking into account 20% of inclusion failure, it is necessary to include 26 individuals per group a total of 52 subjects.

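### Sections 2.4.1 and 4.1 define the primary responder differently on the VAS route (40% improvement versus 40% and a 40 mm fall), and nothing says which governs

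*Protocol*

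**What the plan says.** Protocol section 2.4.1 (Primary Endpoint) sets the rule as "responders in case of at least 40% improvement in VAS or ODI at month 24 compared to baseline". It has no millimetre condition.

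Protocol section 4.1 (Primary Outcome Measures) sets the rule for the same endpoint at the same time point. On pain it reads: "The clinical response is defined as pain relief of at least 40% and 40 mm decrease on VAS scale between baseline and month 24". A second route, through disability, then follows in that sentence: "or 40% improvement of functional index ODI at month 24 compared to baseline". The pain route therefore carries two conditions joined by *and*, while the disability route matches that of 2.4.1. The same section describes the instrument as a "VAS pain scale (0 – 100, where 0 represents no pain and 100 represents the worst pain imaginable").

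Eligibility (section 3.1) requires "Pain baseline > 40 mm on VAS (0- 100").

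The sample size (section 7, repeated in the synopsis) rests on the statement that "a responder rate is expected at 12 months of the order of 30% in controls and 68% for MSC". It does not say which responder rule those rates describe.

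**The concern.** A binary primary endpoint needs one rule that classifies every patient. Here there are two, both in force, and nothing ranks one above the other. Patients whose pain falls by at least 40% but by less than 40 mm, and whose ODI improves by less than 40%, change status with the section that is applied.

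The primary result could then depend on a choice between definitions made after the data are seen. The planning rates are also hard to interpret, since a rate of 30% or 68% means something different under each rule. With 26 patients per arm, each reclassified patient moves that arm's responder rate by 1/26 = 3.8 percentage points.

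**Working it through.** **Inputs.** VAS range 0-100 (section 4.1); entry above 40 mm (section 3.1); the two responder rules (sections 2.4.1 and 4.1); planning rates 30% and 68%, power 80%, alpha 5%, 1:1 allocation, 20% inclusion failure, 26 per group (section 7).

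**The plan's own figure.** With p1 = 0.30, p2 = 0.68 and pooled p = 0.49, the standard formula is

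n = [z_alpha × √(2 × 0.49 × 0.51) + z_beta × √(0.30 × 0.70 + 0.68 × 0.32)]² / 0.38².

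- Two-sided 5%: [1.960 × 0.707 + 0.842 × 0.654]² / 0.1444 ≈ 25.96, so 26 per arm before any allowance for losses.
- One-sided 5%: [1.645 × 0.707 + 0.842 × 0.654]² / 0.1444 ≈ 20.3, so 21 per arm. Then 21 × 1.2 = 25.2, rounded up to 26.

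The stated 26 with its 20% allowance is thus reached under a one-sided test. Sidedness is not stated; that is a separate matter and the present point does not depend on it. What matters here is that the calculation takes the two rates as given and ties them to neither rule.

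**Step 1: the 40% condition in 4.1 never binds.** Let B be the baseline VAS in mm. A 40 mm fall is a relative improvement of 40/B. Since B cannot exceed 100, 40/B ≥ 40/100 = 40%. Every patient with a 40 mm fall therefore already has at least 40% relief, and the 4.1 VAS route reduces to a fall of at least 40 mm. This reads *at least* as covering both thresholds, which is the natural reading.

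**Step 2: the rules are nested and differ over nearly the whole entry range.** Section 2.4.1 needs a fall of 0.4 × B; section 4.1 needs 40 mm. Because 0.4 × B ≤ 40, every 4.1 VAS responder is a 2.4.1 VAS responder, but not the reverse.

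| Baseline (mm) | Fall needed, 2.4.1 (0.4 × B) | Fall needed, 4.1 | Relief this implies under 4.1 (40/B) |
|---|---|---|---|
| 41 | 16.4 mm | 40 mm | 97.6% |
| 45 | 18 mm | 40 mm | 88.9% |
| 50 | 20 mm | 40 mm | 80.0% |
| 60 | 24 mm | 40 mm | 66.7% |
| 70 | 28 mm | 40 mm | 57.1% |
| 80 | 32 mm | 40 mm | 50.0% |
| 100 | 40 mm | 40 mm | 40.0% |

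On a continuous scale the two VAS thresholds meet only at a baseline of 100 mm.

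**Step 3: enumeration.** Take whole-millimetre baselines from 41 to 100 and follow-up values from 0 up to baseline. Pairs with a 40 mm fall but less than 40% relief: 0. Pairs with at least 40% relief but a fall below 40 mm: the sum over B of (40 − ⌈0.4 × B⌉) = 2,400 − 1,716 = 684. The disagreement runs in one direction only. This counts possible score pairs; it does not estimate how many patients will fall among them.

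**Step 4: one patient, two answers.** Baseline 60 mm, month 24 at 30 mm, ODI improvement below 40%. The fall is 30 mm and the relief 30/60 = 50%. Under 2.4.1, 50% ≥ 40%: responder. Under 4.1, 30 mm < 40 mm and ODI does not qualify: non-responder.

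**The case against.** The strongest defence is that 4.1 is simply the detailed form of 2.4.1. The rules are nested, not opposed, and the ODI route is shared, so any patient with 40% ODI improvement is classified the same way by both. Entry above 40 mm also makes a 40 mm fall arithmetically possible for every patient eligible on that score, so neither rule shuts anyone out. All of this is correct. It narrows the conflict to the VAS route but does not remove it: 2.4.1 does not defer to 4.1, and the two give different answers for the patient in Step 4. Nor can the millimetre condition be read as restating the percentage, because the two coincide only at a baseline of 100 mm.

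Three stronger readings are tempting, and the documents do not support them.

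- A reader might infer that patients entering just above 40 mm need almost complete pain relief to count as responders. That is true of the 4.1 VAS route only; 40% ODI improvement is enough without it.
- A reader might infer that 4.1 makes baseline severity drive the endpoint. That depends on how pain changes. If falls in millimetres do not depend on baseline, the chance of a 40 mm fall is the same at every baseline, and it is the percentage rule whose threshold rises with baseline. If relief is proportional to baseline, the pattern reverses. The protocol has no data to decide between these.
- A reader might want a figure for lost power or changed response rates. That would need VAS and ODI means, standard deviations and their correlation, none of which the protocol gives.

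**Conclusion.** The point holds as an internal contradiction in the primary endpoint, confined to the VAS route. Section 4.1 is a stricter rule nested in 2.4.1, and its 40% condition is redundant. Moving from 2.4.1 to 4.1 can only lower each arm's responder rate or leave it unchanged. By how much, and whether the difference between arms grows or shrinks, cannot be derived from the protocol. The size that can be stated is the gap in thresholds (16 versus 40 mm at a baseline of 41 mm, narrowing to none at 100 mm) and the 3.8 percentage points that each reclassified patient is worth in an arm of 26.

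The conclusion rests on the 0-100 range, on entry above 40 mm, and on *at least* governing both thresholds in 4.1. The documents do not show which version was intended. Nor can the 30% and 68% rates be assumed to belong to either: section 7 attributes them to literature at 12 months, while both responder rules apply at month 24.

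**What to change.** Before unblinding, make sections 2.4.1 and 4.1 state one identical responder rule. The choice of threshold is the sponsor's.

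- If the 40 mm condition is kept, add it to 2.4.1 and drop the redundant 40% VAS criterion from 4.1.
- If the percentage rule is kept, remove the 40 mm condition from 4.1.
- In either case, name the other version as a prespecified sensitivity analysis.

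Then trace the 30% and 68% rates to their source and record which definition and time point they describe. If these do not match the chosen month-24 rule, restate the assumed rates, or the power at 26 per group, in section 7 and in the synopsis.

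The cost is a sentence or two in 2.4.1 and 4.1, a check of the planning source with a possible revision of the sample-size text, and the amendment procedure. No new data are needed, since VAS and ODI are already scheduled at Day 0 and month 24.

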### **4.2 Secondary Outcome Measures**

**Disability and quality of life evolution** include Short Form (SF)-36 scores, global assessment by the patient and the physician. Overall pain intensity in the lumbar spine (1 = none, 2 = mild, 3 = moderate, 4 = severe, 5 = extreme); patient's global assessment of disease activity (1 = very good, 2 = good, 3 = fair, 4 = poor, 5 = very poor); physician's global assessment of disease activity (1 = very good, 2 = good, 3 = fair, 4 = poor, 5 = very poor) will be performed at 0, 3, 6, 12 and 24 months.

Additionally we will assess: de-/increase in rescue painkillers medication. Rescue medication use will be recorded throughout the study duration by a diary file. During the treatment phase of the study, a daily maximum of 3 g

paracetamol/acetaminophen will be permitted. Opioid intake will be possible if paracetamol/acetaminophen is not sufficient. Only tramadol will be authorized.

## **Pain**

The measurement of pain will be determined by self-report of current pain in rest and in motion in the low back pain using a VAS scale. In brief, the VAS consisted of a 10 cm horizontal line anchored with descriptors of pain including "no pain" on one end (left) and "extreme pain" on the other (right). After sitting for 10 minutes, subjects struck a vertical line through the 10 cm VAS representing their CP, and the distance from left end (no pain) to the vertical line was recorded in centimetres. In addition, the patients will fill VAS tests indicating the amount of pain experienced at rest, and in motion.

The drug consumption of painkillers will be assessed throughout the study at each visit. A diary file containing doses, drug name and indication will be given to each patient. The investigator will control this book at each visit. A reduction in dose or frequency of administration of painkillers is an indirect marker of the benefits of MSC therapy.

**Employment and work status** will be assessed. For this we will assign each of the patients to one of 4 categories designated as "employable" which included those who were unemployed due to pain, employed but on sick leave, laid off, or working. The other categories include retired, disabled, and elderly at least 60 years of age, eligible for social security.

**Structural assessment:** Evolution of affected disc(s) by quantitative Magnetic Resonance Imaging (MRI) density measurements in T2 and T1spin/echo and T1rho weighted images performed at 0, 6 12 and 24 months used as an indication of disc fluid and GAG content. The "quality" of the patient's lumbar disc will be monitored non invasively using T2weighted MRI sagittal images (Orozco et al., 2011) and, in T1spin/echo MRI. Lumbar disc grading will be performed in the sagittal T2 weighted images by two physicians independently who were experienced in MRI of the spine. They will review each intervertebral disc from L1–2 to L5-S1 by the modified Pfirrmann criteria. The modified Pfirrmann grading system assesses degenerated intervertebral discs by MRI for the asymmetry in disc structure, distinction of the nucleus and the annulus, signal intensity of intervertebral discs and height of intervertebral discs and assigns grade 1 to 8 for disc degeneration (Table by Griffin et al. Spine 2007).

**Table 1. Modified Grading System for Lumbar Disc Degeneration\***

| Grade | Signal From Nucleus and Inner Fibers of Anulus                          | Distinction Between Inner and Outer Fibers of Anulus at Posterior Aspect of Disc | Height of Disc                   |
|-------|-------------------------------------------------------------------------|----------------------------------------------------------------------------------|----------------------------------|
| 1     | Uniformly hyperintense, equal to CSF                                    | Distinct                                                                         | Normal                           |
| 2     | Hyperintense (>presacral fat and <CSF) ± hypointense intranuclear cleft | Distinct                                                                         | Normal                           |
| 3     | Hyperintense though <presacral fat                                      | Distinct                                                                         | Normal                           |
| 4     | Mildly hyperintense (slightly >outer fibers of anulus)                  | Indistinct                                                                       | Normal                           |
| 5     | Hypointense (= outer fibers of anulus)                                  | Indistinct                                                                       | Normal                           |
| 6     | Hypointense                                                             | Indistinct                                                                       | <30% reduction in disc height    |
| 7     | Hypointense                                                             | Indistinct                                                                       | 30%-60% reduction in disc height |
| 8     | Hypointense                                                             | Indistinct                                                                       | >60% reduction in disc height    |

\*Grades 1, 2, and 3 are based on the signal intensity of the nucleus and inner fibers of anulus. For Grade 4, the margins between the inner and outer fibers of the anulus at the posterior margin of the disc are indistinct. For Grade 5, the disc is uniformly hypointense, although there is no loss of disc space height. For Grades, 6, 7, and 8, there is progressive loss of disc space height. These could be broadly classified as mild, moderate, to severe loss of disc space height. Very occasionally, although obvious disc collapse is present, hyperintense signal from the nucleus and inner fibers of the anulus is preserved. This is referred to by a double entry, e.g., 4/7, with the former reporting the disc signal and the latter the degree of collapse.

